## Methods/Design

The ABC-program is evaluated in a prospective, multicenter, randomized wait-list controlled trial (RCT), in a ratio of 1:1, to be allocated to the intervention group or a waiting-list control group. The RCT was undertaken after a first-time pilot study from 2009–2011 where 405 parents were recruited, after which the ABC-program and questionnaires included were slightly modified. Parents with children 3–12 years old in the municipalities and city districts taking part in the RCT-study will be asked to participate further, from 2012–2014. Those who accept participation after receiving verbal information and providing written informed consent, will be randomized to receive the ABC-program either directly or after six months (on a waiting-list). Parents randomized to a delayed-onset ABC-program starting after 6 months compose the control group. There will be approximately 300 parents each in the intervention and control group, respectively. Follow-ups are employed 6 and 12 months after baseline (See Figure 1).

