**Figure 2 F2:**
[figure not shown]
The ABC-RCT CONSORT flow diagram.

Parents participating in the trial received incentives during and after the trial. After completion of the first follow-up questionnaire, parents received entrance for the whole family to an open-air museum located in the city of Stockholm. About the same time, parents in the control group received a chocolate bar (parents in the first wave) and reflectors (parents in the second wave). When the final follow-up questionnaire has been conducted, 12 months after the baseline, parents will receive a gift card offering them either a paperback book or three movie rentals.

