### Measures

Time points of primary interest for all outcome measures are at baseline, two weeks after intervention, and six months after baseline for both intervention and control groups. In the intervention group only, a twelve month follow-up will be conducted. A minor group of parents and children will be observed, to explore any changes in the dyadic interaction between parent and child after taking part in the ABC-program. Video recordings of both a mealtime and a play situation will be collected at baseline and at six months after baseline.

In the survey questionnaire, parents provide information about their gender, marital status, number of children, birth country, educational level, monthly income, child’s age, and gender, birth country for the child, and child care. The questionnaires included in the survey are described below.

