### Analysis

Analyses will be conducted both with intention-to-treat-analyses as well as study-completer-analyses. The statistical analyses will be performed according to best practice guidelines for evaluating effects in RCTs [39]. This may come to include MANOVA, repeated measures ANOVA, and regression analyses. Cohen’s *d* will be included to calculate effect sizes. The importance of some of the parental characteristics will also be evaluated in relation to the 6-month-outcome – in other words, the moderator as well as the mediation relations. To do this, the definition by Baron and Kenny [40] for a mediational relation will be used: Evaluate 1) whether there is a significant correlation between the independent and dependent variables, 2) if the independent variable and possible mediator are significantly related, and 3) if the mediator and dependent variable are significantly related. Since the waitlist group was offered the intervention after six months, pre- to post- data for intervention and waitlist groups will also be combined to improve power in the secondary analyses.

Data collected in the trial will also be used to evaluate the possible cost-effectiveness of ABC. The cost-effectiveness analysis (CEA) [41] will include costs, savings, and health gains of the children. Calculations will be performed from the societal perspective meaning that the intention is to consider all costs and consequences. The foundation of the CEA will be an incremental analysis to investigate the extra costs, potentially extra savings and health gains of ABC in relation to the control group. The costs will include resources needed for running the ABC-program such as project staff salaries, parents’ time, materials, and meeting arrangements. The time spent on learning and performing the ABC-program will be based on information from contact persons at the local agencies involved in the study. The health gains will be reported in gained Quality Adjusted Life Years (QALYs), which will be estimated by potentially-improved scores on the HRQOL among children pre-intervention, immediately post-intervention, and 6- and 12 months post-intervention. A sensitivity analysis will be performed to explore the uncertainty of the study result.

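### The cost-effectiveness analysis is incremental against the control group but uses QALY time points that the schedule does not supply: no untreated comparison exists beyond 6 months after baseline

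*Protocol article*

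**What the plan says.** The Analysis section of the protocol article describes an incremental analysis meant to "investigate the extra costs, potentially extra savings and health gains of ABC in relation to the control group". It then says that health gains will be expressed as QALYs, estimated from "HRQOL among children pre-intervention, immediately post-intervention, and 6- and 12 months post-intervention". The underlying score is a parent-proxy visual analogue scale from 0 to 100, listed under Secondary outcome measures without a schedule of its own.

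The schedule is given elsewhere:

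- Measures, for all outcome measures: "at baseline, two weeks after intervention, and six months after baseline for both intervention and control groups".
- Measures, next sentence: "In the intervention group only, a twelve month follow-up will be conducted".
- Methods/Design: "Follow-ups are employed 6 and 12 months after baseline".
- The paragraph on incentives after Figure 2: "When the final follow-up questionnaire has been conducted, 12 months after the baseline".
- Methods/Design, on the comparator: "Parents randomized to a delayed-onset ABC-program starting after 6 months compose the control group".

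The research questions under Aims also count months from baseline.

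**The concern.** An incremental QALY is a difference between arms in quality of life accumulated over time. It needs a measurement in both arms at each time point used, and correct dates for those measurements. The Analysis section names a comparator and a set of time points that the schedule does not provide together.

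The main fault is the 12-month point. Only the intervention group is measured then, and by that time controls may already have had the program. If the 12-month intervention scores go into the QALY gain, the result over that stretch no longer rests on randomization.

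The lesser fault is the time anchor. The Analysis section counts 6 and 12 months from the end of the intervention, whereas every other section counts from baseline. Dates multiply directly into QALYs, so an analyst who followed that sentence literally would stretch the area under the curve.

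Cost-effectiveness is research question 6, and the Background links it to how scarce resources are allocated. The cost per QALY is therefore a figure that others may act on.

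**Working it through.** The protocol states no QALY figure to reproduce, so the check is of dates and availability, followed by one illustration of size.

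**1. Which arm is measured when** (Measures; Methods/Design)

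| Time | Intervention | Control | Control untreated? |
|---|---|---|---|
| Baseline | yes | yes | yes |
| Two weeks after the program | yes | yes | yes |
| 6 months after baseline | yes | yes | yes, program starts after this |
| 12 months after baseline | yes | none scheduled | no |

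The last row of the randomized, untreated comparison is 6 months after baseline, that is 0.5 year. Changing the anchor does not alter this.

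**2. Where the stated time points would fall**

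Inputs from Intervention: four sessions, one every other week. First to last session = 3 intervals × 2 weeks = 6 weeks. The lag from baseline to session 1 is not stated; I assume 0 to 8 weeks. One month = 365.25 / 7 / 12 = 4.348 weeks.

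- 6 months post-intervention = 6 + (lag + 6)/4.348 months after baseline. Lag 0: 6 + 1.38 = 7.38. Lag 8: 6 + 3.22 = 9.22.
- 12 months post-intervention: 13.38 to 15.22 months after baseline.

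The first falls after the 6-month visit and after controls become eligible for the program. The second falls after the final questionnaire. Neither visit is in the schedule.

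**3. Illustration of mis-dating**

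Assume that the between-arm gain rises linearly to g at month 2 and then stays at g.

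- Area over months 0 to 6: 0.5 × 2g + 4g = 5g.
- Same scores, with the 6-month visit placed at month 8 (2 + 6): 0.5 × 2g + 6g = 7g.
- Ratio 7/5 = 1.40, or 40% too large.

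Sensitivity to the unstated lag, with the gain reached at the test two weeks after the last session and the 6-month visit dated from that last session:

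- Lag 0: test at (0 + 6 + 2)/4.348 = 1.84 months. Correct area 0.92g + 4.16g = 5.08g; mis-dated 0.92g + 5.54g = 6.46g; ratio 1.27.
- Lag 8 weeks: test at 16/4.348 = 3.68 months. Correct area 1.84g + 2.32g = 4.16g; mis-dated 1.84g + 5.54g = 7.38g; ratio 1.77.

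The inflation thus runs from about 27% to 77% over the assumed lags. It applies to the magnitude of a difference of either sign.

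**4. Weight of the uncontrolled period**

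If the same gain g were credited for months 6 to 12, it would add 6g to the 5g of the randomized period: 6/11 = 55% of the 12-month total with no control measurement behind it.

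Suppose instead that the control group's 6-month value is carried forward, and let c be the change that untreated children would have shown between months 6 and 12, taken as linear. The area error is then 0.5 × 6 × c = 3c. The documents give neither the size nor the sign of c.

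**The case against.** Four points can be made for the protocol.

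- **The anchor is most likely a slip.** One sentence counts from the intervention and all others count from baseline. Nothing shows that analysts would place the 6-month questionnaire at month 8. This stands: the 27% to 77% range describes what literal use of the sentence would do, and is not an error that the protocol is known to commit.
- **The text does not say that 12-month intervention scores will be set against a control value.** They could be meant to inform persistence, and a sensitivity analysis is announced. Measures also makes the time points up to 6 months the ones of primary interest. This stands in part. The sentence still lists 12 months among the sources of the QALY gain in an analysis defined against controls, and the sensitivity analysis is generic: nothing says that the 12-month part is uncontrolled.
- **Wait-list data will be pooled with intervention data.** The Analysis section limits this to secondary analyses, and the post-program data come from parents who have had the program. They cannot act as an untreated 12-month control.
- **A journal article condenses.** That would excuse silence. Here the article states time points and a comparator that conflict with its own schedule.

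Two stronger readings are tempting. A reader might infer that the uncontrolled 12-month data favour the program because children improve with age. No section says that the parent-proxy score rises with age; untreated change could be upward, downward or nil. A reader might also infer that research question 3, which reaches to 12 months, fails for the same reason. It asks whether attendance and use of components relate to effects, which can be answered as an association within the intervention group.

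**Conclusion.** The point holds in a limited form. As written, the incremental QALY analysis cannot be carried out as a randomized comparison over its stated horizon. The comparison with untreated controls ends 6 months after baseline, and this conclusion needs no assumption beyond the published schedule. Quality-of-life data at 12 months would enter uncontrolled, with a bias whose direction cannot be told from the documents.

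The conflict over the time anchor is real but probably a matter of wording. The 40% figure is an illustration that rests on an assumed shape of gain, an assumed post-test at month 2, and literal use of the sentence.

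This should be corrected before the economic analysis is run, but it does not threaten the trial's main result. Cost-effectiveness is a secondary aim, and the primary outcomes (parental self-efficacy and child health and development) are untouched.

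**What to change.** Three changes to the economic paragraph of the Analysis section:

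1. State the quality-of-life time points as baseline, two weeks after the program, and 6 and 12 months after baseline, and compute areas from actual questionnaire dates.
2. Define the primary incremental cost per QALY over baseline to 6 months, where both arms are measured and controls have not started the program.
3. Report any result that uses 12-month data as a labelled extrapolation scenario. Say that there is no 12-month control measurement, and state what is assumed about persistence of the effect after month 6.

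The cost is a few sentences and one scenario analysis, with no new data collection. The downside is that the headline horizon shortens to 6 months, so any longer-term case for the program rests openly on assumptions.

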### Ethics

This study obtained ethical approval from the Regional Ethics Committee at the Karolinska Institutet (Registration number: 2012/93-31/5). The same committee gave ethical approval to the amendment, including video-recorded observations of parents and children (Registration number: 2012/2184-32).

### Working groups

#### Research group

A research group including an associate professor in clinical psychology, two doctors of medicine, and two PhD students was established to conduct the trial. The competences of the group comprised knowledge of child mental development, public health, parenting programs, health promotion, health economics and experience conducting and evaluating randomized controlled trials.

#### Method group

Responsible for the delivery and implementation of the method and training of group leaders, was a group of three registered psychologists within family and social welfare in the City of Stockholm. The group also had the main responsibility for the development of the ABC-program, although in consultation with the research group in the early stages. This approach was based on earlier research that has demonstrated larger effects when evaluations are performed by implementers of an intervention [42,43].

#### Steering group

Beyond parts of the research and method groups, the steering group also consisted of representatives from two of the participating municipalities/city districts. The aim of the group was to monitor the process of the trial.

#### Reference group

In the reference group, members of the research group participated, as well as ABC developers and the contact person for each municipality/city district. Additionally, a representative from the County Administrative Board in the County of Stockholm was included. A main task for the reference group was to disseminate information to all involved municipalities/city districts.

### Adjustments

In the first recruitment wave, the baseline measure consisted of a paper questionnaire. For the second wave, a web-based questionnaire was introduced as a complement. This resulted in about one-third of the baseline measures for the second wave being conducted online. Most of these web-based questionnaires were completed by parents who could not attend the information meeting.

## Discussion

This paper describes the protocol for a randomized controlled trial evaluating the effectiveness of a Swedish universal parenting group program, ABC (All Children in Focus/Alla Barn i Centrum (Swed.)). All Children in Focus aims at improving children’s health and development, and includes four 2.5 hour structured sessions for parents with children aged 3–12 years old. Except for the quantitative outcome measures to evaluate the effectiveness of ABC, the protocol also describes health economic and qualitative analyses of the program. The inclusion of several methodologies in the evaluation of ABC contributes to a deepened knowledge and understanding of potential use of ABC in the future, as well as for future evaluations of universal health-promotion parenting programs.

The design of this study is a randomized controlled trial with a waitlist control group. This type of evaluation can raise concern over some practical considerations. Especially in the case of working with other professionals in addition to researchers, the practitioners in our study were concerned about parents entering the control group, and having to wait six months to get the intervention. It is important for all involved in the study to understand the ethics and the reasoning for this. As described from earlier pragmatic trials on child mental health interventions conducted in Wales, there are some factors which can contribute to participation by service settings, such as early involvement, and clarification of requirements and contributions of both researchers and the service settings [44]. In the trial of ABC, most practitioners were involved at an early stage since they participated in the pilot studies of the intervention; only three of the participating municipalities and city districts were newly introduced to the randomized trial when it started. Before the trial started, all contact persons were informed about what the municipality/city district had to contribute to the trial (e.g., group leaders, premises, recruitment of parents), and all group leaders were informed about the trial. In this manner, participating municipalities/city districts were involved, and clarification could be made where it was needed to prevent future confusion about expectations.

The training and tutoring of group leaders was performed either by two ABC instructors, or by the method group. It is crucial that all group leaders are trained and tutored in a similar way, as was done for this trial. To measure fidelity to the program, video recordings of the group leaders will be used, performed by themselves (in a few cases one of the researchers supplied the group leaders with the equipment). The group leaders had to sign a consent form that they were willing to participate in recording of one session. Initially, some of the group leaders expressed concern about the recordings, but they were convinced about the advantages by other group leaders who had already tried this in the pilot study. So far, two pairs of group leaders have not video-recorded any session, which has been due to a mistake in communication, and problems with the recording equipment. Also, for some pairs of group leaders, the whole sessions were not recorded due to trouble with the equipment; in addition, a few group leaders recorded another session than the one randomized for the group.

When recruiting parents, all involved in a project must be aware of what the research trial implicates and what it means for those participating. As an example, some parents expressed that they wanted to participate together with a friend or a neighbor. Parents should be informed about the study procedure at an early stage to avoid confusion; for example, not all participants will receive the intervention directly, but may be assigned to a waiting-list control. In this trial, there was confusion about the study procedure for some parents.

To increase the possibility of a high response rate in the study, incentives were used in the form of free family entrance to an open-air museum after the first follow-up, and also a chocolate bar or reflectors for the waiting-list subjects. For the last follow-up, a gift certificate for either a paperback book or movie rental is distributed. Less than half of the families took advantage of the entrance to the open-air museum when this was offered; it is uncertain to what extent these incentives may have influenced the response rate.

Some of the outcome measures included in this study, such as GHQ or PPI, have mainly been used to assess reduction of problems or symptoms rather than the increase of strengths or positive behaviors. In health promotion research more instruments measuring positive aspects of health would be worthwhile.

Most of the existing parenting programs [7-12] tend to focus on treatment or prevention of different child behavior problems. Other parenting programs, which are offered at a universal level [16,17,25], seem to have a more pathogenic approach, meaning that they focus on prevention of ill-health or problems rather than having a salutogenic perspective with focus on promotion of health. This study will thereby add knowledge in the field of health promotion regarding the potential value of a universal health promotion parent group program.
